#### Criteria for discontinuing or modifying allocated interventions {11b}

As far as ophthalmic lenses are a non-invasive treatment, the only criterion for discontinuing the study will be that participants are not able to adapt to the design of the lenses (either control or intervention spectacle lenses). However, any participant is free to leave the study without any reason.

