### Sample size {14}

Based on an annual progression of − 0.50D, an estimated minimum efficacy of 50% compared to control, a power of 80%, an alpha of 5%, and a standard deviation for objective refraction of 0.70D, the size of the sample is 124.

Taking possible dropouts into account, 150 children will be included in the intervention group and 150 children in the control group.

Assignment to the different groups will be made by stratified randomization based on the age and spherical equivalent of the child. Randomization will be done automatically at the patient level by including the parameters of the initial visit in the eCRF. The researchers from the clinics will have partial access to the eCRF so that they will only be able to access the data that they have entered or must complete, not knowing the group assigned for each child.

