#### Plans to promote participant retention and complete follow-up {18b}

To promote participant retention:All participants have been assigned to one investigator who is in contact with the participants and their parents during the whole study, solving any problems (broken spectacles, blurred vision, etc.).In addition, annual reports will be done for parents to know the evolution of myopia.Parents are also informed that all the children belonging to the control group that completes the 2-year study will be offered a spectacle to control myopia.

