### Methods in analysis to handle protocol non-adherence and any statistical methods to handle missing data {20c}

To minimize these problems, an “intention-to-treat analysis” will be done as the primary analysis, with a per-protocol analysis as a secondary/supplementary analysis.

Data management includes the query management process made by the CRO. Data validation will be automatic during the data capture done by the investigator. Figure 2 shows the data entry and validation flowchart.

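### Children who cannot adapt to the lens are discontinued from the study with no stated outcome follow-up, so the intention-to-treat primary analysis is not secured

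*Protocol article*

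**What the plan says.** Four places in the protocol article bear on this point.

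- **Criteria for discontinuing or modifying allocated interventions {11b}.** The heading concerns the intervention, but the text says that "the only criterion for discontinuing the study will be that participants are not able to adapt to the design of the lenses". A parenthesis applies this to both kinds of lens. The next sentence allows voluntary withdrawal at any time.
- **Methods in analysis to handle protocol non-adherence and missing data {20c}.** An intention-to-treat analysis "will be done as the primary analysis, with a per-protocol analysis as a secondary/supplementary analysis". It is introduced as the way to keep these problems small. The section then turns to query management.
- **Statistical methods {20a}.** Efficacy is analysed on a full analysis set and a per-protocol set. The full analysis set is neither defined nor linked to intention-to-treat. The analysis plan is to be finalised before data lock.
- **Sample size {14}.** After arriving at 124, the text continues: "Taking possible dropouts into account, 150 children will be included in the intervention group", with the same number for control. No drop-out rate is given.

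In Table 1, cycloplegic autorefraction is done at screening and then at V3 (6 months), V4, V5 and V6. Nothing is scheduled specifically for children who have stopped the lens.

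**The concern.** An intention-to-treat comparison needs outcomes from every randomised child, including those who stop the allocated lens. Section {11b}, read literally, sends exactly those children out of the study. They go for a reason tied to the lens itself, and the two lenses differ: one imposes simultaneous defocus and the other is conventional single vision. Equal rates of failure to adapt cannot be taken for granted, although the article gives no evidence that they differ.

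Section {20c} then treats intention-to-treat as a remedy for missing data, which it is not: it supplies no value for an absent outcome. If non-adapters' outcomes are not collected, the primary result drifts towards the effect in children who tolerate the lens while still carrying the intention-to-treat label.

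**Working it through.** **1. The plan's own sample size.** Inputs from {14}: "Based on an annual progression of" −0.50 D; "an estimated minimum efficacy of 50% compared to control", so a difference of 0.50 × 0.50 = 0.25 D; "a standard deviation for objective refraction of 0.70D"; 80% power; 5% alpha, taken as two-sided.

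n per arm = 2 × [0.70 × (1.960 + 0.842) / 0.25]² = 123.07, rounded up to 124. The statement that "the size of the sample is 124" therefore reproduces, as a number per arm. There is no sample-size error behind this point.

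**2. The loss allowed for.** 1 − 124/150 = 17.3%, or 26 children per arm and 52 of 300. With 124 per arm left, power for 0.25 D is 80.3%, but that is power for the difference among those who remain. Extra numbers do not make the remaining children representative.

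**3. What an early leaver contributes.** The first post-baseline refraction is at 6 months. A child who fails to adapt and leaves before then has no post-baseline value of the primary outcome. Any later statistical method must then rest on assumption for that child. A missing-at-random model would not by itself correct this, because such a child has no post-baseline refraction to inform it.

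**4. Size of the shift, in general.** Let f be the share leaving an arm and D the leavers' mean annual progression minus the stayers'. The difference (control minus study) among stayers exceeds the difference among all randomised children by

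f(study) × D(study) − f(control) × D(control).

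This is near zero when f × D is similar in both arms. It is positive (overstatement) when study-lens leavers progress faster than study-lens stayers, and negative when the same happens only in controls.

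**5. Illustration for non-adapters.** Assumption, not in the article: a share f of the study-lens arm leave and would progress like controls (D = 0.25 D/year), while control leavers do not differ from control stayers. The stayers show 0.25 D/year, the intention-to-treat difference is 0.25 × (1 − f), and the overstatement is f/(1 − f).

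| f | Difference among stayers | Intention-to-treat difference | Overstatement |
|---|---|---|---|
| 5% | 0.25 | 0.2375 | 5% |
| 10% | 0.25 | 0.2250 | 11% |
| 15% | 0.25 | 0.2125 | 18% |

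**6. Wider range.** With loss in one arm only, f from 5% to 17.3% and D from 0.10 to 0.50 D, the shift f × D runs from 0.005 to 0.087 D, which is 2% to 35% of the 0.25 D target. All values of D are assumptions.

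**The case against.** The strongest reply has four parts.

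*The wording of {11b} may be loose.* Its heading is about the intervention, withdrawal has its own sentence, and no text says that visits cease when the lens is stopped. This is possible. It is also why a reader might infer too much in saying that intention-to-treat cannot be delivered: follow-up after stopping is not forbidden. But the printed text names the study, not the lens, and a site following it has no instruction to keep the child in follow-up.

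*Missing-data methods belong in the analysis plan.* This stands for the choice of model and sensitivity analysis; their absence from a condensed article is no fault. It does not cover data collection, because an analysis plan cannot restore refractions that were never taken. Nor does it cover the misstatement in {20c} of what intention-to-treat does.

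*The tests are not restricted to completers.* This stands. A reader might infer that the named tests use completers only, but {20a} does not say so. Because the outcome is mean annual progression and refraction is taken four times after baseline, a child leaving after 6 or 12 months could still contribute. The problem is sharpest for those who leave before V3.

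*Selective loss of fast-progressing controls is speculative.* This also stands. Section {18b} says that "annual reports will be done for parents to know the evolution of myopia", and a reader might infer that parents of fast-progressing controls would withdraw them. But the same section offers myopia-control spectacles to control children who complete two years, and {17a} states that participants are blinded. The article gives no reason for progression-driven loss in controls alone, and if it acted equally in both arms the shifts in step 4 would largely cancel.

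**Conclusion.** The point holds as a conflict between {11b} and {20c}: one takes non-adapters out of the study, and the other relies on an analysis that needs their outcomes and presents that analysis as a remedy for missing data. The intention-to-treat estimate is not secured; the documents do not support saying that it is unattainable.

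The overstatement of 5 to 18% rests on two assumptions with no source in the article: that 5 to 15% of the study-lens arm leave, and that they would progress like controls. Equal rates of loss alone would not guarantee freedom from bias, but similar loss with a similar relation to progression would leave it small. The 17.3% is implied by the sample size, not stated as an expected rate.

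This should be fixed. It bears on the primary estimate and the change is small, but the size of the bias is unknown and may be slight.

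**What to change.** Reconcile {11b}, {20a} and {20c}.

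- **{11b}:** separate stopping the lens from leaving the study. State that children who stop the lens keep the scheduled refraction and axial-length visits (V3 to V6) and are analysed as randomised, unless consent is withdrawn. This concerns outcome collection only; when a child should stop the lens is a clinical matter on which this point takes no position.
- **{20c}:** state that intention-to-treat defines who is analysed and in which group and does not itself handle missing values. The missing-data model and a sensitivity analysis for departures from it can sit in the analysis plan.
- **{20a}:** define the full analysis set and tie it to intention-to-treat.

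The cost is a protocol amendment, communicated as {25} requires, and visits already scheduled for what is probably a small number of children. Enrolment ended on 25 May 2023, so children who have already left are not recovered by new wording.

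There is also a cost in power. If non-adapters are followed and gain no benefit, 150 per arm with complete follow-up gives 83.6% power at 5% non-adapters, 79.5% at 10% and 72.5% at 17.3%, against 87.1% with none. That is the power for the comparison the protocol calls primary.

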#### Strategies to improve adherence to interventions {11c}

An external CRO has created the electronic case report form (eCRF) and is responsible for giving access with different permissions to all the researchers and clinicians involved in the study. They also monitor the data included in the eCRF and ask the clinician for modifications or explanations when needed.

All the clinics will be also monitored in the different visits by an internal committee from Universidad Complutense de Madrid and ISEC Lisboa to ensure they adhere to intervention protocols.

#### Relevant concomitant care permitted or prohibited during the trial {11d}

There are no restrictions regarding concomitant care during the trial.

#### Provisions for post-trial care {30}

It is highly recommended that children with myopia have follow-ups every year to know the evolution and to check if spectacles need to be replaced. Children can follow up with their visits to the clinics and opticians that are going to participate in this clinical trial.

### Outcomes {12}

#### Primary outcome

The primary outcome is to compare the mean annual progression of the spherical equivalent between myopic children treated with ZEISS MyoCare lenses and those who wear a conventional single-vision lens.

#### Secondary outcomes

The following are the secondary outcomes:Compare the mean annual progression of axial length between myopic children treated with ZEISS MyoCare lenses and those who wear a conventional single-vision lensCompare the proportion of children in which the annual increase in the spherical equivalent does not exceed 0.5D in each of the groups (treatment and control)Compare the proportion of children in which the annual increase in axial length does not exceed 0.22 mm in each of the groups (treatment and control)Analyze twice a year the progression of myopia by studying the changes in the spherical equivalent, the axial length, the thickness of the choroid, the phorias, and the accommodative delay of both groups (control and treatment)Evaluate the progression of the axial length and the spherical equivalent according to the age and graduation of the children at the beginning of the treatment in both groups (control and treatment)

### Participant timeline {13}

Table 1 shows the schedule of the different protocol phases: enrollment, follow-up visits, data collection, and assessment that were designed following the Standardized Protocol Items: Recommendations for Interventional Trials (SPIRIT) guidelines. The study flowchart is shown in Fig. 1.

### Sample size {14}

Based on an annual progression of − 0.50D, an estimated minimum efficacy of 50% compared to control, a power of 80%, an alpha of 5%, and a standard deviation for objective refraction of 0.70D, the size of the sample is 124.

Taking possible dropouts into account, 150 children will be included in the intervention group and 150 children in the control group.

Assignment to the different groups will be made by stratified randomization based on the age and spherical equivalent of the child. Randomization will be done automatically at the patient level by including the parameters of the initial visit in the eCRF. The researchers from the clinics will have partial access to the eCRF so that they will only be able to access the data that they have entered or must complete, not knowing the group assigned for each child.

### Recruitment {15}

For the recruitment of children, data from the myopia prevalence studies carried out by this research group since 2016 will be used. Since 2016, more than 12,000 children between 5 and 7 years of age have been screened, with a 17% prevalence of myopia [27, 28]. Children who have progressive myopia and have not been previously treated with any treatment to control myopia from the participating clinics, as well as those myopes followed up in the school’s screenings that we made annually in Lisbon, will be also included.

### Assignment of interventions: allocation

#### Sequence generation {16a}

The randomization has been programmed with minimization using 3 study variables for group stratification of sex, age group, and objective refraction group (spherical equivalent):Sex (2 options): male/femaleAge (2 options): 6–9 years/10–13 yearsSpherical equivalent (6 options): [− 0.5, − 1.25], [− 1.25, − 2], [− 2, − 2.75], [− 2.75, − 3.5], [− 3.5, − 4.25], [− 4.25, − 5]

The values will be computer-generated and assigned to the patients as A for the control group and B for the study lenses, with a 1:1 ratio.

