**Methods:**

A 2-year prospective, multicenter, randomized controlled, and double-blind clinical trial is used to investigate the efficacy of a new design of ophthalmic lenses to slow the progression of myopia. Three hundred children aged from 6 to 13 years old will be recruited and randomly assigned to a study or control group. The study group will be composed of 150 children wearing MyoCare while the control group will be composed of 150 children wearing Clearview. The inclusion criteria will be myopia with a spherical equivalent between − 0.75D and − 5.00D, astigmatism < 1.50D, and anisometropia < 1.00D and having a historical evolution of at least − 0.50 The primary outcome is to compare the mean annual progression of the spherical equivalent between both groups. The secondary outcomes are axial length, choroidal thickness, phorias, and accommodative status of both groups.

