#### Intervention description {11a}

Children assigned to the study group will wear ZEISS MyoCare lenses, while those assigned to the control group will wear conventional ZEISS ClearView single-vision lenses in their spectacles. Both lenses will be made of the same material (MR8) and hard as well as anti-reflection coating (ZEISS DuraVision Platinum) and will have the same surface treatments.

The following is the general overview:Subjective refraction (endpoint: best visual acuity with the most positive sphere).Objective refraction after cycloplegia (mean of 3 measurements).Ocular biometry (five measurements using IOLMaster 700 (Carl Zeiss Meditec AG, Jena, Germany)).OCT: spectral domain OCT using volume scan (and enhanced depth imaging) to visualize the choroid (ZEISS CIRRUS 5000, Carl Zeiss Meditec AG, Jena, Germany or Spectralis de Heildebergd Engineering) for 6 × 6 mm^2^ area. The choroidal thickness will be evaluated by automatic segmentation.Slit lamp examination.Intraocular pressure.Fundus check.Parameters of wear.Monocular measurement of distance and near visual acuity.Peripheral visual acuity.Distance phoria, near phoria @ 33 cm, and accommodative lag @ 33 cm.Vision quality, visual comfort, quality of life, and frequency of visual symptoms with lens wear are to be graded by the subjects themselves through questionnaires.

Table 1 describes the different measurements taken in each of the visits.

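### The protocol states the allocation rule in two conflicting ways (stratified on age and spherical equivalent; minimised on sex, age and spherical equivalent), and the planned group comparison adjusts for none of these factors

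*Protocol article*

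**What the plan says.** Three places in the Protocol article bear on how a child is allocated.

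- **Sample size {14}**: "Assignment to the different groups will be made by stratified randomization based on the age and spherical equivalent of the child". The section adds: "Randomization will be done automatically at the patient level by including the parameters of the initial visit in the eCRF".
- **Sequence generation {16a}**: "The randomization has been programmed with minimization using 3 study variables for group stratification of sex, age group, and objective refraction group". It lists two sex classes, two age classes (6–9 and 10–13 years) and six SE classes, all written with closed brackets: -0.5 to -1.25, -1.25 to -2, -2 to -2.75, -2.75 to -3.5, -3.5 to -4.25 and -4.25 to -5 D. Children are "assigned to the patients as A for the control group and B for the study lenses, with a 1:1 ratio".
- **Eligibility criteria {10}**, with the same range in the abstract: "spherical equivalent between − 0.75D and − 5.00D".

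Under Implementation {16c}, inclusion criteria are checked at the screening visit, and the allocation is generated only once the screening pages of the eCRF are complete.

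Under Statistical methods {20a}, groups are compared with a t-test or Wilcoxon test for quantitative endpoints and a chi-square or exact test for categorical ones. A linear regression is planned separately, to study how age and refraction at the start relate to annual change.

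**The concern.** Stratified randomisation and minimisation are different procedures. The first usually runs a separate random list in each stratum. The second assigns each child according to the running totals of each factor level. The two sections also name different factors, because sex appears only in {16a}. A reader cannot tell which procedure was run.

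This matters for the analysis, which should account for the factors that were balanced. If those factors predict progression and the analysis ignores them, the estimated standard error of the group difference is generally too large. A statistician working from Sample size {14} would leave out sex. One who tried to rebuild the SE class from {16a} could not place a child who lies exactly on a cut-point.

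**Working it through.** **1. The two statements side by side**

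| | Sample size {14} | Sequence generation {16a} |
|---|---|---|
| Method | stratified randomisation | minimisation |
| Factors | age, SE | sex, age group, SE group |
| Structure, using the {16a} classes | 2 × 6 = 12 strata, 300/12 = 25 children each on average | 2 + 2 + 6 = 10 factor levels to balance (24 cells of 12.5 if fully crossed) |

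The wording of {16a} presents minimisation as a means of stratifying, which softens the conflict over the method. Nothing softens the conflict over sex.

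**2. SE classes**

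Six adjoining classes, each closed at both ends, share five cut-points: -1.25, -2, -2.75, -3.5 and -4.25 D. Every other eligible value falls in exactly one class, and no eligible value falls in none.

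The number of children on a cut-point cannot be derived, because the document gives neither the recording step nor the distribution of SE. The share of *possible values* that are cut-points depends entirely on the assumed step:

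- 0.25 D: 5/18 = 28%
- 0.125 D: 5/35 = 14%
- 0.125/3 D (a mean of three readings, each in 0.125 D steps): 5/103 = 5%
- 0.01 D: 5/426 = 1%

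These are shares of values, not of children. Intervention description {11a} lists "Objective refraction after cycloplegia (mean of 3 measurements", which favours the finer steps if that is the reading used for allocation.

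**3. First class against eligibility**

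The class from -0.5 to -1.25 D is 0.75 D wide. The eligible part, from -0.75 to -1.25 D, is 0.50 D wide, so 0.25 D lies outside the eligible range. Eligible values weaker than -1.25 D belong to this class only, so the bound creates no ambiguity.

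**4. Sample size**

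The inputs are an annual progression of 0.50 D, "an estimated minimum efficacy of 50% compared to control" (a difference of 0.25 D), SD 0.70 D, 80% power and two-sided alpha of 5% (the protocol does not state sidedness):

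n per arm = 2 × (1.960 + 0.842)² × 0.70² / 0.25² = 123.1, rounded up to 124.

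This reproduces the protocol's 124. No allocation factor enters the formula, so the figure does not depend on which statement is right.

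**5. What the unadjusted test does**

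Let R² be the share of the variance of progression explained by the balanced factors. With close balance on them, the true standard error of the difference is about √(1 − R²) × √(2 × SD²/n). The t-test reports √(2 × SD²/n). With SD 0.70 D and 124 per arm, the reported value is √(2 × 0.49/124) = 0.089 D, and the true value is 0.089 × √(1 − R²). The unadjusted test is therefore conservative by an amount that depends on R², which the document does not give. Age and baseline refraction are plausibly prognostic: the secondary outcomes include progression according to both.

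**The case against.** The strongest case on the other side is that this is a small reporting slip. The {14} sentence is a summary under another heading. The {16a} item is the dedicated place, is more specific, and describes what has been programmed. Allocation is automatic, so the program resolves any tie in some definite way. Boundary handling is a coding detail that a condensed article may leave to the full protocol. No analysis in {20a} uses the SE class, and the unseen statistical analysis plan may already specify an adjusted model. Enrolment is complete, and no bias is shown.

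Much of this stands. {16a} is the likelier account, the defect lies in the stated rule and is not shown in the conduct, and the cut-points alone would be minor. It does not remove the conflict over factors: both sentences are positive statements, so condensation does not explain the difference. Nor does it change the fact that the tests {20a} names for the group comparison are unadjusted.

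Three stronger readings are tempting and are not supported:

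- **That the plan leaves the class of children in general undetermined.** Only a child exactly on one of five values has two printed classes. The conflict between the sections concerns method and factors, not class.
- **That children weaker than -0.75 D would be allocated because a class admits them.** Eligibility is checked at screening under {16c}, before allocation; the class limits are not the eligibility check. {10} also does not say which refraction it means, while {16a} uses objective refraction and Table 1 lists three refractions at screening. The two limits may not refer to the same measurement.
- **That the shares of values can be turned into a number of children.** This would need an even spread of SE and a known recording step, and the document gives neither.

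**Conclusion.** The contradiction on allocation factors and method is firm: {14} and {16a} cannot both be right as written. The five shared cut-points and the -0.5 D bound are lesser drafting faults. The first leaves the printed class open for an unknown number of children, and the second leaves it open for none.

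The consequence for inference is loss of precision, not bias. The standard error of an unadjusted comparison is overstated by the factor 1/√(1 − R²), with R² unknown. This assumes that allocation achieved close balance on the factors and that they predict progression. The sample size of 124 per arm, the recruited 150 per arm and the 1:1 ratio are unaffected.

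**What to change.** 1. Confirm the method and the factors from the eCRF allocation program.
2. Correct the sentence in Sample size {14} to match, including sex if it was used. If the program differs from {16a}, correct that section too.
3. Print the six SE classes in {16a} as coded, with one open end each, and name the refraction that feeds them.
4. Reconcile or explain the -0.5 D bound against Eligibility criteria {10}, without altering the record of what was coded. Moving the printed bound to -0.75 D when the program used -0.5 D would misreport the allocation.
5. For the group comparison of progression, specify a model adjusted for the allocation factors actually used: sex and age, with baseline SE either as a continuous covariate or as the class stored by the eCRF. Do not rely only on the unadjusted tests in {20a}.

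The cost is one check of the program, a few corrected sentences and one model specification, to be settled before the data are locked. Nothing changes for enrolled children, and no further recruitment is needed.

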## Methods: participants, interventions and outcomes

### Study setting {9}

The clinical trial is being done in the following ophthalmologic clinics in Spain and Portugal: Novovision (Madrid and Murcia, Spain), Virgen de Lujan clinic (Seville, Spain), Instituto clínico quirúrgico de Oftalmología—ICQO (Bilbao, Spain), Instituto de Microcirugía Ocular—IMO (Madrid, Spain), and Clínica Privada de Oftalmologia – CPO (Lisbon, Portugal). The trial is being coordinated by Universidad Complutense de Madrid and Instituto Superior de Educação e Ciências, ISEC Lisboa. Ethical approval was obtained from the Ethics Committee CEIm Hospital Clínico San Carlos. Written informed consent was collected from the parents/guardians and participants older than 12 years old before the enrolment. Table 1 shows the schedule of the different protocol phases: enrollment, follow-up visits, data collection, and assessment that were designed following the Standardized Protocol Items: Recommendations for Interventional Trials (SPIRIT) guidelines. The study flowchart is shown in Fig. 1.

**Table 1 Tab1:** Schedule of assessments and examination items

Date/item		Screening	Spectacles dispense	Follow-up					
		Day − 30 to day 0	V0	V1	V2	V3	V4	V5	V6
			Day 0	1 week ± 1 day	3 months ± 15 days	6 months ± 30 days	12 months ± 30 days	18 months ± 30 days	24 months ± 30 days
Informed consent signed		X							
Basic information	Demographics	X							
	History	X							
Refraction	Noncycloplegic autorefraction	X				X	X	X	X
	Subjective refraction	X				X	X	X	X
	Cycloplegic autorefraction	X				X	X	X	X
Visual acuity	Uncorrected visual acuity	X				X	X	X	X
	Best-corrected visual acuity	X				X	X	X	X
	Central visual acuity		X		X	X	X	X	X
	Peripheral visual acuity		X		X				
Eye examination	Keratometry	X				X	X	X	X
	Slit lamp examination	X				X	X	X	X
	Fundus examination	X							
	Intraocular pressure measurement	X							
	Axial length	X			X	X	X	X	X
	Choroidal thickness	X				X	X	X	X
Binocular vision	Accommodative LAG	X				X	X	X	X
	Monocular estimated method (MEM) retinoscopy	X				X	X	X	X
	Phoria (distance and near)	X				X	X	X	X
Spectacle fitting	Frame position and lens condition		X						
Questionnaires	Lifestyle	X							
	Spectacle lens performance and wearability		X	X	X

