### Statistical methods for primary and secondary outcomes {20a}

The statistical analysis of this study will be made by a statistician who will participate in the entire process of study design, implementation, data management, analysis of study results, and summary. Once the study protocol and CRF are completed, the statistical analysis plan will be finalized before the study data is locked to complete the statistical analysis report.

Statistical analysis will be performed using Stata. The statistical description and inference of the data will be based on the characteristics of the data and the selection of applicable descriptive indicators and hypothesis testing methods.

Efficacy analyses will be performed based on the full analysis set and per the protocol set. All baseline demographic analyses will be performed based on the analysis set.

The data included will be analyzed using the applicable statistical methods according to their distribution characteristics. Unless otherwise specified, quantitative endpoints will be described by calculating the mean, standard deviation, median, minimum, maximum, lower quartile (Q1), and upper quartile (Q3), and the categorical assessments will be described by calculating the number and percentage of subjects. Quantitative endpoint cluster comparisons will be performed using the cluster *t*-test, or Wilcoxon rank sum test depending on the data distribution, and categorical endpoint cluster comparisons will be performed using the chi test—square or the exact probability test.

For studies of the evolution of the progression of myopia, ANOVAs of repeated measures or Kruskal–Wallis tests will be performed.

Finally, to study how the age and graduation of the child at the start of treatment are affected, a linear regression model will be built to assess the annual change in myopia and axial length analyzing data from the right eyes of all children, what is a standard practice in this kind of studies [29–32].

All statistical tests will be determined to be statistically significant based on *P* < 0.05.

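### Clinic is neither a minimisation factor nor a term in the planned group comparisons; a linear model with clinic would be a cheap improvement with a small gain in precision

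*Protocol article*

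**What the plan says.** Study setting {9} introduces the sites with "The clinical trial is being done in the following ophthalmologic clinics in Spain and Portugal" and lists six: two in Madrid and one each in Murcia, Seville, Bilbao and Lisbon. Recruitment {15} draws on the group's prevalence studies and on patients of the participating clinics, and adds children from "screenings that we made annually in Lisbon".

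Sequence generation {16a} describes a minimisation on three variables "for group stratification of sex, age group, and objective refraction group". Sample size {14} says that randomisation is at the level of the individual child and mentions age and spherical equivalent (SE). Neither section mentions clinic or country.

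Statistical methods {20a} states: "Quantitative endpoint cluster comparisons will be performed using the cluster" t-test, or the Wilcoxon rank sum test, depending on the distribution. Categorical endpoints get a chi-square or exact test, and the course over time gets repeated-measures ANOVA or Kruskal–Wallis. A linear regression is planned to study age and refraction at the start of treatment. No clinic term appears in any of these. The same section says that the statistical analysis plan will be final before the data are locked.

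**The concern.** In a multicentre trial, clinics may differ in the average annual change of their patients. Where they do, a two-sample test counts that variation as noise around the lens difference, and a model with clinic removes it. Because clinic is not in the minimisation either, the split between lenses within a clinic is left to chance.

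At stake is the width of the confidence interval for the primary difference, in a trial sized for 80% power. The clinic of each child is already known, so the variation could be removed without new data.

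**Working it through.** **Inputs from Sample size {14}.** "Based on an annual progression of − 0.50D, an estimated minimum efficacy of 50% compared to control" gives a difference of 0.50 × 50% = 0.25 D. The rest is "a power of 80%, an alpha of 5%, and a standard deviation for objective refraction of 0.70D, the size of the sample is 124". The SD of 0.70 D is one overall figure, not split into parts between and within clinics. Sidedness is not stated.

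**The plan's own figure.** n per arm = 2 × (1.96 + 0.8416)² × 0.70² / 0.25² = 2 × 7.849 × 0.49 / 0.0625 = 123.1, which rounds up to 124. The stated 124 is therefore reproduced as children per arm, two-sided (a one-sided test would need 97). The standard error (SE of the difference) is 0.70 × √(2/124) = 0.0889 D, and power is 80.3% by the normal approximation. No clinic component enters.

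**Assumption.** The clinic share of the variance in annual change, ρ, is not in the article. I use 0, 2%, 5% and 10%.

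**Step 1: upper limit of the gain.** If adjustment removed the whole share at no cost, the SD would be 0.70 × √(1 − ρ).

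| ρ | SD (D) | standard error (D) | power at 124 per arm |
|---|---|---|---|
| 0 | 0.700 | 0.0889 | 80.3% |
| 2% | 0.693 | 0.0880 | 81.1% |
| 5% | 0.682 | 0.0866 | 82.3% |
| 10% | 0.664 | 0.0843 | 84.2% |

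**Step 2: why the real gain is smaller.**

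- Adjustment has a cost. With allocation not balanced by clinic, five clinic contrasts raise the variance of the lens difference by about 247/(247 − 5) = 1.021, so the standard error rises by about 1.0%. At ρ = 0 it becomes 0.0889 × 1.010 = 0.0898 D and power falls from 80.3% to 79.5%.
- With only six clinics of unequal size, the realised between-clinic variance in the sample is below the nominal share. For assumed clinic sizes of 83, 66, 41, 25, 20 and 13 (total 248), the sum of squared clinic proportions is 0.23. About 1 − 0.23 = 77% of the nominal share is there to be removed.

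**Step 3: simulation with both effects.** 248 children, those six clinic sizes, normal clinic effects, true difference 0.25 D, 4,000 trials per setting; allocation was random across clinics.

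| ρ | power, t-test | power, model with clinic | gain (points) |
|---|---|---|---|
| 0 | 80.2% | 79.6% | −0.6 |
| 2% | 79.6% | 79.7% | 0.1 |
| 5% | 80.5% | 81.1% | 0.7 |
| 10% | 80.6% | 82.9% | 2.3 |

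A rerun with 20,000 trials per setting gave gains of −0.8, −0.2, 0.4 and 2.4 points. A third simulation put the gain at 5% as high as 1.3 points. The rounded reading is 0, 1 and 2 points for shares of 2%, 5% and 10%.

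**Step 4: type I error.** With no true difference, the unadjusted t-test rejected in 4.5% to 5.6% of simulated trials over the same range of ρ.

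**Step 5: imbalance.** With 300 children in six equal clinics (assumed) and allocation random across clinics, at least one clinic is split 60:40 or worse in about 61% of allocations. With assumed sizes of 100, 80, 50, 30, 25 and 15 it is about 87%. The effect on the lens difference is small: its SD is about √ρ × 0.0889, that is 0.013 D at 2% and 0.028 D at 10%, against a target of 0.25 D. This variation is part of the 0.0889 D that the unadjusted interval already uses.

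**The case against.** The strongest reply is that centre adjustment is routine content of a statistical analysis plan. That plan is not shown, it is to be finalised before data lock, and it could still add clinic. This stands as a limit: the point does not say that the final analysis will omit clinic. But the article does not leave the method open. It names two-sample tests that cannot hold a covariate, so a model with clinic is an alternative to a stated method.

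It is also fair to say that the choice of three minimisation factors is no error and that, with the last child enrolled on 25 May 2023 (Trial status), allocation cannot be changed. Both are accepted.

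A reader might infer more than the article supports:

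- **That a chance imbalance in one clinic biases the result.** It does not. Children are randomised individually, so such an imbalance is random error that the unadjusted interval covers. Counting it as a second harm beside the wider interval would count the same variance twice.
- **That case mix differs between clinics by design.** Recruitment {15} names a Lisbon school route, but the eligibility criteria are the same everywhere and no difference in case mix is stated.
- **That refraction technique differs between clinics.** Nothing says so. The article sets a subjective endpoint, takes the mean of three cycloplegic readings, trains every site and monitors the centres.
- **That the word cluster in the t-test sentence means clinic is already handled.** No clustering unit is named, and the same word is applied to the categorical tests. It most likely means group.

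**Conclusion.** The point holds as a cheap improvement. Clinic is absent from the minimisation, and the group comparisons named for quantitative endpoints cannot include it, so any between-clinic variance in annual change remains in the error term.

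The consequence is a possible modest loss of precision. At 124 per arm, adjustment gains roughly 0, 1 or 2 power points if clinics explain 2%, 5% or 10% of the variance, and loses under 1 point if they explain none. These shares and the clinic sizes are assumptions; the article gives neither. The unadjusted test keeps its planned 80% power and a type I error near 5%, so the article does not support a reading that the primary analysis is invalid or underpowered for this reason.

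**What to change.** In Statistical methods {20a}, replace the two-sample test for annual change in SE and in axial length with a linear model of change on lens group. Include clinic (six levels, fixed effect) and the minimisation factors (sex, age group, spherical equivalent) as covariates. Fix this before data lock, so that the clinic term is not a choice made after seeing results, and show the lens difference by clinic descriptively.

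The cost is a changed primary method in the text and no new data. Clinic takes five of 248 − 2 = 246 residual degrees of freedom. The minimisation factors take up to seven more (1 + 1 + 5, if SE is entered in its six bands). If clinics do not differ, the clinic term costs under 1 point of power.
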